### Sample size

Pregnant women will be recruited and randomly allocated to a control (20 participants) or intervention (20 participants) group. A sample size of 40 pregnant women was chosen based on a previous study we conducted and in which we were able to recruit 40 pregnant women in twelve months [32] and considering that over 4600 women gave birth at the local health services in 2016–2017 (including 1800 at the *CIUSSS-MCQ*) [33]. Furthermore, one of the study goals is to obtain an estimate of variance for the primary outcomes of a full-scale study. A minimally clinical important difference between groups has already been established and it is suggested that 10 to 20 participants per group is sufficient to inform feasibility and to plan for a larger study [34]. Between group differences in LBPP and disability score after the intervention will be used to estimate adequate sample size for future research planning.

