#### Intervention group

Pregnant women in the intervention group will participate in three 40-min exercise sessions per week from ≤ 20 weeks of gestation until 34–36 weeks of gestation: one supervised group session via the Zoom platform (once a month, this session will take place at the *Université du Québec à Trois-Rivières*) and two unsupervised sessions at home.

All sessions will include a 5-min warm-up period followed by specific exercises of moderate-intensity aimed at strengthening muscles of the lumbo-pelvic-hip core complex in order to improve stabilization and alignment of the spine and pelvis (transversus abdominis, internal obliques, multifidus, pelvic floor, thigh, and hip muscles) [36, 37]. The sessions will end with gentle stretching. No specific equipment will be needed to complete the home exercise component of the program. The intervention will be adapted to the stage of pregnancy and related discomfort to ensure a safe, individualized, and yet motivating training experience for each participant. Women will receive a weekly text message with an individually tailored home-exercise program to be completed before the next group session. The text message will contain a link giving access not only to the weekly exercise program, but also to a web-based electronic diary to help participants document their participation in the home exercise sessions (compliance and adverse events), incidence (a painful episode), frequency, and intensity of daily LBPP, as well as any treatment received to prevent and treat LBPP. Participants of this group will also access the same standard prenatal care recommendations as the control group, which includes basic information about what to do when suffering from LBPP, which is provided in the practical guide“ *From Tiny Tot to Toddler”* [35]*.*

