### Data collection

#### Primary outcome measures

##### Feasibility components: recruitment, retention, adherence rate, safety of the intervention, and acceptability

The feasibility of recruitment, evaluated for both groups at the pre-intervention visit, will be defined as the ability to recruit eligible women throughout a 12-month period. The feasibility of obtaining a successful retention rate and consequently low attrition will be assessed using the completion of pre- and post-intervention questionnaires (see below). Adherence to the protocol will be defined as attendance to the supervised group exercise sessions and completion of the unsupervised home exercise sessions. The retention and adherence rates will be evaluated for the intervention group at the post-intervention visit. Safety of the intervention will be determined based on the number of adverse events, which will be defined as symptom flare-ups that will prevent a woman from taking part in subsequent exercise sessions or injuries requiring medical attention. In addition to the kinesiologist taking note of any undesirable effects during supervised exercise group sessions, women from the intervention group will be asked to report, via weekly text messages and their web-based diary, any reaction or flare-up that is not consistent with their usual pain presentation as a result of either home exercise or supervised group exercise sessions. Information concerning adverse events will be collected for the intervention group on a weekly basis throughout the study. Acceptability of the intervention, assessed for the intervention group at the post-intervention visit, will be determined based on how the intervention will be perceived by pregnant women (including satisfaction, practicality and accessibility assessed using 5-point Likert scales).

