**Assessments:**				
***Primary outcomes measures***				
***Recruitment rate***		X		
***Retention rate***				X
***Adherence rate***				X^c^
***Safety of the intervention***			X^c^	X^c^
***Acceptability of the intervention***				X

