***Secondary outcomes measures***				
***LBPP incidence, frequency and intensity***		X	X	X
***Functional disability***		X		X
***Physical activity levels***		X		X
***Fear avoidance behavior***		X		X
***Anxiety***		X		X
***Depression***		X		X

Pre-intervention visit (≤ 20 weeks of gestation); throughout the study (between pre-intervention and post-intervention visits); post-intervention visit (34–36 weeks of gestation)

^a^Standard prenatal care

^b^Motor control exercise program at UQTR and at home as well as standard prenatal care

^c^Intervention group only

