### Statistical analysis

Demographic data will be presented using means and standard deviations. For primary outcome measures (recruitment, retention, adherence rate, safety, and acceptability), means, standard deviations and/or percentage will be presented. For secondary outcomes measures, descriptive statistics will be used to describe within-group changes from baseline visit to post-intervention visit (34-36 weeks of pregnancy). Differences between group in mean change with confidence intervals and effect sizes (Cohen’s *d*) will be reported for each measure.

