### Progression criteria

The following criteria must be met in order to consider progression to a main RCT:Recruitment criteria: recruitment rate of 40 eligible women over a 12-month period.Retention criteria: retention rate of ≥ 80% of recruited women.Adherence criteria: adherence rate of ≥ 75% to the supervised and unsupervised exercise sessions.Safety criteria: less than 25% of women experiencing acute LBPP flare-ups interfering with daily activities.

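### Acceptability, a primary outcome, is collected only at the 34–36-week visit, so intervention women lost before then give no rating and the result is likely to be overstated if some leave because of the programme

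*Protocol article*

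**What the plan says.** The Statistical analysis section lists acceptability among the primary outcomes and plans a descriptive summary: "For primary outcome measures (recruitment, retention, adherence rate, safety, and acceptability), means, standard deviations and/or percentage will be presented".

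The section on feasibility components fixes population and time: "Acceptability of the intervention, assessed for the intervention group at the post-intervention visit". The content is women's perception of the intervention, "including satisfaction, practicality and accessibility assessed using 5-point Likert scales".

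Table 1 has one mark for acceptability, in the post-intervention column, and none in the column for the period between the two visits. Safety, also a primary outcome measured in the intervention arm, is marked in both. The table's footnote places the last assessment at the "post-intervention visit (34–36 weeks of gestation" time point. Entry is at 20 weeks or earlier, so the visit falls at least 34 − 20 = 14 weeks after entry.

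Women are "randomly allocated to a control (20 participants) or intervention (20 participants) group". The Progression criteria accept retention of 80% or more "of recruited women".

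A weekly electronic channel already exists in the intervention arm: "The text message will contain a link giving access not only to the weekly exercise program, but also to a web-based electronic diary". As described, it records home sessions, adverse events, pain and treatments, but not acceptability.

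**The concern.** Whether a woman is asked for a rating can depend on what the rating would be. A woman who finds three sessions a week, or the monthly session at the university, impractical may leave for that reason. She would probably have rated practicality or accessibility low, and under the stated schedule she never receives the form. Losses unrelated to the programme have no such effect, but losses caused by it push the result upward.

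The issue is the time point itself, which is stated in the text and again in Table 1. It does not depend on a detail that a fuller document might supply.

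A feasibility trial is meant to show what needs changing before the full trial. Retention shows how many women were lost, but not whether the programme drove them away. An acceptability score from attenders only could suggest that the programme needs no change when those who disliked it are absent from the score.

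**Working it through.** The article gives no threshold, expected value or precision for acceptability, so there is no figure to reproduce. The check is a bounding calculation.

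**Inputs**
- n = 20 women allocated to the intervention (Sample size).
- m = number lost before the post-intervention visit. The 80% limit applied within the arm gives m = 0.20 × 20 = 4. The criterion refers to recruited women, so 0.20 × 40 = 8 losses are tolerated overall, and m = 8 is the extreme in which all fall in this arm. m = 2 is shown as a milder case.
- x = number of attenders who rate the programme positively. **This is an assumption**, and so is the split of a 5-point scale into satisfied and not satisfied.

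**Formulas**
- Reported share: x / (n − m).
- Share in all allocated, no leaver satisfied: x / n.
- Share in all allocated, every leaver satisfied: (x + m) / n.
- Largest overstatement: x/(n − m) − x/n = reported share × m/n.

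**Main illustration: m = 4, x = 14**
- Reported: 14/16 = 87.5% (Clopper-Pearson 95% CI 61.7–98.4%).
- No leaver satisfied: 14/20 = 70.0% (45.7–88.1%).
- Every leaver satisfied: 18/20 = 90.0%.
- Largest overstatement: 87.5 − 70.0 = 17.5 points (check: 87.5 × 4/20 = 17.5).

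| Leavers who would have been satisfied | Share of all 20 | Reported minus true |
|---|---|---|
| 0 of 4 | 70% | +17.5 points |
| 1 of 4 | 75% | +12.5 points |
| 2 of 4 | 80% | +7.5 points |
| 3 of 4 | 85% | +2.5 points |
| 4 of 4 | 90% | −2.5 points |

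**Other assumed inputs, no leaver satisfied**

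| Lost | Reported | Share of all 20 | Overstatement |
|---|---|---|---|
| 2 | 14/18 = 77.8% | 70% | 7.8 points |
| 2 | 18/18 = 100% | 90% | 10.0 points |
| 4 | 12/16 = 75.0% | 60% | 15.0 points |
| 4 | 16/16 = 100% | 80% | 20.0 points |
| 8 | 9/12 = 75.0% | 45% | 30.0 points |
| 8 | 12/12 = 100% | 60% | 40.0 points |

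**On the 1–5 scale**, with m = 4 and an assumed mean of 4.0 in attenders, the mean in all 20 is (16 × 4.0 + 4 × s)/20, where s is the leavers' mean. This gives 3.4 for s = 1, 3.6 for s = 2 and 3.8 for s = 3.

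**The case against.** A reader might infer three stronger things, and the document supports none of them.

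- *The result will be overstated.* That requires women to be lost, and lost because of the programme. With full retention, or losses for unrelated reasons, there is little or no bias of this kind. The last row of the first table shows a slight understatement.
- *Women who stop exercising go unheard.* Acceptability is assessed in the intervention group at the visit and is not restricted to women who kept exercising. A woman who stopped but attends still rates the programme. Only those lost to the visit are missing.
- *An inflated score could carry the trial forward.* The Progression criteria cover recruitment, retention, adherence and safety, not acceptability. A dissatisfied leaver lowers retention and may lower adherence, and both have thresholds.

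Two further points have force. The confidence intervals in the illustration overlap heavily, so in an arm of 20 the shift is no larger than sampling uncertainty. That uncertainty has no fixed direction, however, whereas programme-related loss has one. Also, counting every non-responder as dissatisfied would misclassify women lost for unrelated reasons and bias the figure downward, so that value can serve only as a bound.

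A full protocol may describe an exit contact. The article nevertheless states one time point in two places, and a plan followed as written collects no earlier rating.

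**Conclusion.** The point holds in a limited form. Acceptability is measured only in intervention women who reach the 34–36-week visit, and it is likely to be overstated if some earlier losses are caused by the programme. With 4 of 20 lost and 14 of 16 attenders assumed satisfied, the overstatement lies between none and about 18 points. With two losses it is at most about 8 to 10 points when 78% to 100% of attenders are positive. The 30 to 40 points at eight losses need every tolerated loss to fall in one arm, among women who would all have been dissatisfied, so they mark an extreme. All these sizes rest on assumed ratings.

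The damage is to the interpretation of a primary outcome and to what the full trial's designers learn from it. The go/no-go rule is not directly affected. The change should be made because it costs little and the likely error has a known direction.

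**What to change.** - **Collection.** Offer the same 5-point Likert items, plus the reason for leaving, to every woman allocated to the intervention, through the existing text/web link, at discontinuation or at 34–36 weeks, whichever comes first. State that the link remains available to women who stop, since the article does not say so. Amend the feasibility components section and Table 1 to match.
- **Reporting.** Give the result with the number of respondents out of all women allocated to the intervention, and show ratings given at discontinuation separately from those given at the visit.
- **Sensitivity analysis only.** Give best-case and worst-case bounds, with non-responders counted first as satisfied and then as not satisfied, and state the cut-off on the scale that defines satisfied.

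Recruitment began in April 2021. For women already lost, a late contact or the reporting change alone would still help.

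**Cost.** One short extra form and a wording change, with no added visit. Some leavers will not answer, ratings at discontinuation reflect shorter exposure than those at 34–36 weeks, and the reported figure may be less favourable.

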#### Secondary outcome measures

The potential effectiveness of the intervention will be assessed using the following clinical outcomes and assessment tools. All secondary outcome measures (i.e., LBPP incidence, frequency and intensity, functional disability and physical activity levels) will be obtained during the pre-intervention (≤ 20 weeks of gestation) and post-intervention (34–36 weeks of gestation) visit at the university laboratory. Fear avoidance behaviors the level of anxiety, and depression will also be assessed pre- and post-intervention, as they are considered potential prognostic factors (and confounding variables) of LBPP [38].

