##### LBPP incidence, frequency, and intensity

Lumbar and pelvic pain presence and intensity will be evaluated using recommended clinical tests [6, 31] and a 100-mm visual analog scale (VAS) [39]. The construct validity of the visual analog scale has been shown to be significantly and positively correlated with other self-reported measures of pain intensity (i.e., 101-point numerical rating scale, 11-point box scale, 6-point behavioral rating scale, 4-point verbal rating scale, and 5-point verbal rating scale) [40, 41]. Furthermore, participants will receive weekly text messages to collect information about the incidence (first episode during pregnancy), frequency (number of days), and intensity of LBPP. The minimal clinically important difference (MCID) for this outcome will be set according to Hagg et al. (2003) who defined the difference in the score change between patients assessing themselves as “better” and those assessing themselves as “unchanged”. The MCID for this outcome will be 18–19 mm on a 100-mm VAS scale [42].

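### Secondary outcomes are summarised as change to a 34–36-week visit, and the weekly pain reports from both arms have no stated role in the analysis

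*Protocol article*

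**What the plan says.** All places are in the protocol article.

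- **Secondary outcome measures:** "All secondary outcome measures (i.e., LBPP incidence, frequency and intensity, functional disability and physical activity levels) will be obtained during the pre-intervention" visit and the "post-intervention (34–36 weeks of gestation) visit at the university laboratory". Fear avoidance, anxiety and depression follow in a separate sentence that names no place. Table 1 marks them in the same two columns, which its note defines as visits.
- **Statistical analysis:** for secondary outcomes, "descriptive statistics will be used to describe within-group changes from baseline visit to post-intervention visit". Between-group differences in mean change follow, with confidence intervals and Cohen's d.
- **LBPP incidence, frequency, and intensity:** "participants will receive weekly text messages to collect information about the incidence (first episode during pregnancy), frequency (number of days), and intensity of LBPP". Table 1 also marks LBPP in the column for the period between the visits, without the footnote that limits other rows to the exercise arm.
- **Feasibility components:** retention is "assessed using the completion of pre- and post-intervention questionnaires". Progression criteria asks for at least 80%.
- **Sample size:** the between-group differences in LBPP and disability will be used to size the future trial.

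**The concern.** The article describes two streams of pain data, and its analysis uses only one of them by name. The stream it names depends on a visit late in pregnancy, which some women will miss. The stream it leaves unnamed can reach a woman without travel.

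Two things follow. First, incidence and frequency are awkward as a change between two visits: a first episode is an event in time, and a number of days is a count over a period. Weekly reports capture both directly. Second, a woman without the end visit has no change score, whatever she reported by text. Late-pregnancy attendance may plausibly depend on pain. If it does, attenders are a selected group, and the differences carried into the next trial's sample size inherit that selection.

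**Working it through.** **The plan's own figure.** The sample of 20 + 20 = 40 rests on earlier recruitment experience and a rule of 10 to 20 per group. No alpha, power, SD or dropout is given, so no formula can reproduce it. What can be checked is what a lost end visit does to the stated analysis.

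**Step 1. Source of each outcome.**

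| Outcome | Visits | Weekly text | Named in the analysis |
|---|---|---|---|
| LBPP incidence, frequency, intensity | yes | yes | visit-to-visit change |
| Disability, activity, fear avoidance, anxiety, depression | yes | no | visit-to-visit change |

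From 20 weeks, weekly reporting gives 34 − 20 = 14 to 36 − 20 = 16 reports per woman, and more for earlier entrants. None has a stated use.

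**Step 2. Loss the plan tolerates.** At 80% retention, 0.8 × 20 = 16 per arm and 0.8 × 40 = 32 overall. This is the progression threshold, used here as a scenario and not as a forecast.

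**Step 3. Bias.** Let m be the share of an arm without the end visit, and D the mean change in missing women minus the mean change in attenders. The full-arm mean is (1 − m) × A + m × (A + D) = A + mD, where A is the attenders' mean. Reporting A is therefore wrong by mD, and the between-group difference is wrong by m₁D₁ − m₂D₂. The values of D are assumptions; 18–19 mm is included because it is the article's MCID.

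| Gap D (mm) | 20% lost in one arm, none in the other | 20% and 10% lost, same D | 20% lost in both, same D |
|---|---|---|---|
| 10 | 2.0 | 1.0 | 0 |
| 18 | 3.6 | 1.8 | 0 |
| 19 | 3.8 | 1.9 | 0 |
| 30 | 6.0 | 3.0 | 0 |

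Against the MCID, the one-arm range runs from 2/19 = 11% to 6/18 = 33%. Equal loss cancels only if D is also equal in the two arms.

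**Step 4. Precision.** The 95% half-width for the between-group difference, in SD units, is t(0.975, 2n − 2) × √(2/n). It is 0.640 for n = 20 and 0.722 for n = 16, a ratio of 1.128. The standard error alone grows by √(20/16) = 1.118. For assumed SDs of 20, 25 and 30 mm, the half-width goes from 12.8, 16.0 and 19.2 mm to 14.4, 18.1 and 21.7 mm.

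**The case against.** The strongest reply is that this is a 40-woman feasibility study with a descriptive secondary analysis, reported in a condensed article. Handling of missing outcomes, follow-up after stopping exercise and any repeated-measures model may sit in the full protocol or SAP, and their absence here is not a fault. The between-group sentence does not expressly exclude the weekly data. A shift of 2–6 mm is also small beside a half-width of 14–22 mm at 16 per arm.

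Much of this stands, and it rules out several stronger readings:

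- *Pain is measured only at the laboratory.* It is not; weekly texts collect it as well.
- *Women who stop exercising lose their outcomes.* Nothing in the article links stopping exercise to ending follow-up or bars these women from the end visit.
- *Retention measures ability to travel.* Retention is defined by questionnaire completion, not attendance, and the article does not forbid completion off site. It simply does not say whether that is possible.
- *The bias favours exercise.* The direction depends on who is missing in each arm, which is unknown.
- *Zoom and the web diary could fill the gap in both arms.* They are described for the exercise arm only; for controls the article shows only the weekly texts.
- *The weekly score can replace the visit value.* The article does not say that the weekly intensity uses the 100-mm VAS.

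The reply leaves untouched what the article itself states: where the outcomes are obtained, that they are summarised as visit-to-visit change, and that the weekly series is collected without a stated purpose in the analysis.

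**Conclusion.** The point holds in a limited form. As stated, the analysis depends on the 34–36-week visit, the weekly LBPP reports have no role in it, and the article does not say which source defines incidence, frequency or intensity. If missing the visit depends on pain, the LBPP and disability differences meant for planning the next trial are biased. Size and direction are unknown. For pain the shift is 0.2 × the gap when 20% of one arm is lost, hence 2–6 mm for assumed gaps of 10–30 mm, falling towards zero if loss and gap are similar in both arms. Losing 20% in each arm also widens the confidence interval by about 13%. The gaps and SDs are assumptions; only the 20 per arm, the 80% threshold and the 18–19 mm MCID come from the article. The consequence is modest for the feasibility aim, but the change is cheap and improves the data passed to the full trial.

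**What to change.** 1. **Feasibility components and Secondary outcome measures.** State that any woman in either arm who cannot attend, whether or not she is still exercising, may complete the self-report measures at 34–36 weeks through a web link sent by text, and that she then counts as retained. Record the mode of completion. Only the clinical tests, height and weight need the visit.
2. **LBPP incidence, frequency, and intensity, and Statistical analysis.** State which source defines each LBPP outcome, and take incidence and frequency from the weekly reports. Use the same intensity scale in the texts as at the visits, or analyse the weekly scores separately. Report a repeated-measures estimate of pain intensity up to 34–36 weeks from all randomised women, alongside the visit-to-visit change.

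The cost is mainly wording, a link sent through the existing texts, some mixing of completion modes and slightly more analysis work. The weekly series can recover pain only. Disability, activity, fear avoidance, anxiety and depression depend on the off-site questionnaires in item 1.
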